#### Level 1: Individual Eligibility

Each individual participant within an adult cisgender SMM couple must meet the following individual-level eligibility criteria for the P3 pilot RCT: (1) currently identifies as male and was assigned male at birth (ie, cisgender); (2) be aged ≥18 years; (3) has access to a web-connected device (eg, smartphone, laptop, tablet, or computer); (4) lives in and plans to live in Lima, Peru, for the next 6 months; (5) reports being in a relationship with another cisgender, SMM partner and defines their partner as *someone they feel emotionally or romantically committed to above all others, such as a partner, husband, boyfriend, etc*.; (6) reports being in their relationship for a minimum of 3 months; (7) reports having had CAS with their relationship partner within the previous 3 months; (8) one of the relationship partners reports having had CAS with a casual sex partner in the same timeframe; (9) reports to having no history (ie, within prior 3 months and ever) of intimate partner violence; (10) reports not being coerced by their partner (or others) to participate in the study and related activities; (11) reports feeling safe in the current relationship to participate in the study and related activities; and (12) indicates willingness to test for HIV and other STIs at a local community–based organization at baseline and at 6 months after baseline.

Except for level 1 eligibility criterion number 8, individuals who do not meet all other above-mentioned criteria, will be deemed ineligible, thanked for their interest in the study, and provided a list of HIV and STI prevention resources and other health and relationship-oriented resources that are available in Lima, Peru. Individuals who meet all other criteria (other than number 8) will be prompted to complete an e-consent and enter complete contact information of themselves and their partner. Then, partner 2 will receive a study invite via WhatsApp, which will provide them with access to the eligibility screener and e-consent (if applicable). Level 2 eligibility criteria will automatically be evaluated once both partners complete the eligibility screener.

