### Randomization

An allocated randomization block of 2:2, via an embedded algorithm within the P3 DHI, will be used to randomly assign couples to one of the following 2 intervention conditions following the baseline assessment: (1) an immediate intervention condition where couples will be able to use the P3 DHI for 6 months or (2) a 3-month delayed intervention condition where couples will be able to use the P3 DHI for the last 3 months of the trial. For ethical reasons, a delayed control condition was chosen for the trial study to provide all couples with access to the intervention while also permitting the ability to compare outcome differences between trial arms for the first 3 months of the pilot RCT. In sum, all couples in the pilot RCT will have access to use the P3 DHI for a minimum of 3 months, which will enable data pooling of the entire couple sample (N=60; ie, first 3 months for the immediate intervention condition plus the last 3 months with the delayed intervention condition). The study design will also enable the examination of long-term effects of the P3 DHI (ie, effects after 6 months of use) on outcomes and their use of the P3 DHI among couples randomized to the immediate intervention condition (n=30). Randomization will be blinded to couples but not to the study staff (administrators).

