Preliminary efficacy will be assessed by considering changes in couples’ outcomes A to D over time. For the immediate intervention arm, the differences in outcomes A to D will be observed between receipt of the intervention and subsequent follow-up assessments at 3 months and 6 months (n=30). For the waitlist arm, the differences in outcomes A to D will be observed between receipt of the intervention after the 3-month assessment and subsequent follow-up assessment at month 6 (n=30). As such, this study will be able to pool and combine data from the 30 couples from the immediate intervention arm with data from the 30 couples from the waitlist arm to observe changes in outcomes (ie, from A-D) over a 3-month time period (N=60). Furthermore, through this study, we will also be able to observe changes in couples’ outcomes (ie, from A-D) for a longer period of time (6 months) for the immediate intervention arm (n=30). Comparisons in couples’ outcomes A to D by trial arm (immediate arm vs waitlist arm) will occur between baseline and month 3. In summary, the design we chose for the proposed 6-month pilot RCT is advantageous for 3 reasons: (1) it will allow us to compare differences between immediate intervention and delayed intervention arms for 3 months; (2) it will allow us to make comparisons within the delayed arm from no intervention before to intervention after (months 3 to 6) the assessment; and (3) it will facilitate generating additional intervention data that can be pooled from the immediate and delayed intervention arms to obtain more robust estimates of intervention effect size to more accurately estimate sample size and power for an efficacy RCT in the future.

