#### Power, Sample Size, and Effect Size Estimations

All power calculations were performed with PASS 2020 [59]. For the couple-level analyses, with 60 couples randomized to 2 arms (30 couples in each), for outcome C, we will have 80% power to detect a difference of 0.75 SDs of the mean relationship functioning measure (large effect [60]) using a linear model. For the dichotomous outcomes A and B, we will have 80% power to detect an absolute difference of 35% between the intervention and delayed conditions using a chi-square test. Our power increases for the outcomes analyzed at the individual level, where the correlation between individuals within a dyad must be considered (ie, the interdependence of individuals nested within dyads). For the incidence rate of outcome D assuming Poisson distribution, 30 couples in each arm will have 80% power to detect a difference of 50% rate reduction in STI rate (including HIV) between the intervention and delayed conditions at 6 months assuming a within-pair coefficient of variation between clusters at 0.25 and the intraclass correlation coefficient as high as 0.1 (even higher ICCs do not reduce rate reduction measure in a significant or meaningful way magnitude wise). For all analyses, the α level was set at .05 with 95% CI. This is a feasibility and acceptability trial that is only powered to detect large effects; however, if effect sizes are lower than hypothesized, we will use that information to properly power a large-scale RCT.

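### The pooled N=60 before/after change is more precise but uncontrolled, so it is not a more robust effect size for planning the efficacy RCT

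*Protocol article*

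**What the plan says.** The Aim 3 section of the protocol article defines within-arm changes after receipt of P3. For the immediate arm the change runs from baseline. For the delayed arm it is the change "between receipt of the intervention after the 3-month assessment and subsequent follow-up assessment at month 6 (n=30"). The two sets of 30 couples are then combined to look at change in outcomes A to D "over a 3-month time period (N=60"). The Randomization section describes the same pooling of the immediate arm's first 3 months and the delayed arm's last 3 months, made possible because every couple has at least 3 months of access, "which will enable data pooling of the entire couple sample".

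The Aim 3 section lists three advantages of the design. The first is the between-arm comparison; elsewhere in the section, comparisons "by trial arm (immediate arm vs waitlist arm) will occur between baseline and month 3". The third is the pooled data, whose stated purpose is "to obtain more robust estimates of intervention effect size to more accurately estimate sample size and power for an efficacy RCT in the future".

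**The concern.** A before/after change in people who all receive the intervention estimates the effect plus whatever would have changed anyway. In this trial the delayed arm's months 0 to 3 show what happens without P3, and the pooled set leaves exactly that period out. Nothing in the article subtracts it from the pooled figure or adjusts that figure for period.

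The protocol itself gives several reasons for change without P3:

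- All participants are asked to test for HIV and STIs at baseline, and routine testing is one of the strategies counted in outcome A.
- Nearly all behavioural and relationship measures are repeated at every visit.
- Level 1 eligibility requires CAS with the partner in the prior 3 months, and that "one of the relationship partners reports having had CAS with a casual sex partner in the same timeframe". CAS, part of outcome D, is therefore open to regression to the mean.
- The two pooled windows differ in calendar time and in prior study contact, so they need not estimate the same quantity.

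At stake is the sample size of the next trial. If the pooled figure is used for its stated purpose, the efficacy RCT is planned on effect plus background change.

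**Working it through.** **1. The plan's own figure.** The power section gives 80% power for 0.75 SD with 30 couples per arm at α=.05. A two-sided two-sample t calculation gives 81.5%, so the figure reproduces. It refers to the between-arm comparison and is not in dispute. The article gives no figure for the pooled estimate.

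**2. What each estimate contains.** Let δ be the P3 effect over 3 months, g the background change per 3-month window, and r the regression to the mean, taken to act in months 0 to 3 only. All are in SD units.

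- Immediate arm, months 0 to 3: δ + g + r
- Delayed arm, months 3 to 6: δ + g
- Pooled, equal arms: δ + g + r/2
- Delayed arm, months 0 to 3, untreated: g + r
- Randomised month-3 contrast: (δ + g + r) − (g + r) = δ

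The pooled bias is g + r/2. The documents give no value for g, r or the correlation ρ between visits, so the values below are assumptions. The sample is the planned 60 couples.

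**3. Precision.** The SE of the pooled change is √(2(1−ρ)/60). The SE of the between-arm difference in change is √(4(1−ρ)/30), and with baseline adjustment (ANCOVA) it is √(2(1−ρ²)/30).

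| ρ | Pooled change | Between-arm change | ANCOVA |
|---|---|---|---|
| 0.5 | 0.129 | 0.258 | 0.224 |
| 0.6 | 0.115 | 0.231 | 0.207 |
| 0.7 | 0.100 | 0.200 | 0.184 |

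The pooled change is clearly more precise. That is the only property in which it is better.

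**4. Effect on the next trial.** Per-arm size at 80% power and two-sided 5% is n = 2(2.80/d)², rounded up (2.80 is 1.96 + 0.84; 2.8016 unrounded). Take a true effect of 0.3 SD. True power at the planned n is Φ(0.3√(n/2) − 1.96).

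| Bias in planning value | d used | n per arm | True power |
|---|---|---|---|
| none | 0.30 | 175 | 80% |
| +0.15 | 0.45 | 78 | 47% |
| +0.30 | 0.60 | 44 | 29% |
| −0.10 (adverse) | 0.20 | 393 | 99% |

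A bias of +0.15 arises, for example, from g = 0 and r = 0.3 (0 + 0.3/2). A bias of +0.30 arises from g = 0.3 and r = 0, or from g = 0.2 and r = 0.2.

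**5. An alternative that uses all visits.** Take a linear model for a continuous outcome with three categorical visits, a P3-access indicator (0 for the delayed arm at baseline and month 3, 1 at month 6; 0 then 1, 1 for the immediate arm), ρ = 0.6 and 30 couples per arm. The generalised least squares SE of the access effect is 0.191 SD, or 0.200 with an added arm term. The month-3 ANCOVA gives 0.207 and a plain month-3 t test √(2/30) = 0.258. The period-adjusted model therefore recovers a little precision over ANCOVA without taking background change into the effect.

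**The case against.** The strongest reply is that the pooled data are additional. The between-arm comparison is listed first among the advantages. The Primary Analyses section compares the arms on outcomes A, B and D and tests the arm-by-time interaction for C. This stands. A reader might infer that pooling discards the trial's randomised control; it does not, and the lack of control is confined to the pooled estimate.

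A reader might also take the power section's remark, "we will use that information to properly power a large-scale RCT", as confirming that the next trial will be sized on the pooled figure. In context that remark follows between-arm effect sizes, so it does not support that reading. The point rests on the Aim 3 rationale and on the pooling described under Randomization.

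No pooled significance test is described, so a false-positive rate for such a test would be a property of something the plan does not propose. A fuller analysis plan might adjust the pooled model for period. But the article defines the pooled set as on-intervention changes only, and the mixed model it describes, given for outcome C, has arm, time and their interaction without a time-varying access term.

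Two further limits stand. It is tempting to say that the next trial would come out too small, but background change can go either way. Regression to the mean is supported only for CAS, because entry does not select on A, B or C, and it should act mainly in the first window, which roughly halves its share of the pooled figure.

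**Conclusion.** The claim of greater robustness is wrong as written. The pooled N=60 change is more precise, but it estimates effect plus background change, and it omits the untreated period that would separate the two. It is therefore a poor planning value for the efficacy RCT, the use the article gives it.

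The documents fix neither the size nor the direction of the bias. The range of 78 to 44 per arm, with 47% to 29% power against the 175 needed, is an illustration for a true effect of 0.3 SD and a favourable bias of 0.15 to 0.3 SD; adverse drift would make the next trial too large. The randomised comparison within this pilot, and any conclusion drawn from it, is not affected.

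**What to change.** 1. Take the planning effect size, with its CI, from the randomised baseline-to-month-3 contrast.
2. To use all visits, fit a mixed model with categorical visit and a time-varying P3-access indicator, with a link suited to each outcome: binary for A and B, continuous for C, count for self-reported CAS in D. Report it beside the month-3 contrast, because it assumes similar effects after 3 and 6 months of access. The SEs above apply to a continuous outcome only.
3. Label the pooled before/after change as descriptive and remove the claim that it is more robust.
4. For HIV/STI biomarkers, tested only at baseline and month 6, state that neither the pooled 3-month change nor a randomised month-3 contrast is available. By month 6 both arms have had P3, so no controlled planning effect size comes from them.

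The cost is a change of wording and one model on data already collected. The article reports that data collection has ended and analysis is under way, so the change can still be made. The price is a wider interval for the planning value than the pooled change would show.

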#### Primary Analyses

For outcomes A to D, descriptive statistics will be used to characterize the sample at each time point during the trial (baseline, month 3, and month 6), and by trial arm and couples’ HIV serostatus. Descriptive statistics will also be used to summarize cohort characteristics, relationship functioning variables, and sexual behaviors by the trial arm and by couples’ HIV serostatus. For couples, dyadic data will be calculated if there are no missing values from either partner. For continuous variables, couple-level mean variables will be generated by taking the averaged value from both partners’ scores. For within-dyad variables, couple-level differences will be generated by taking the absolute difference between each of the partner’s scores. Categorical dyadic variables will be generated based on whether both partners had the same or different answers. Two-sample 2-tailed *t* tests and chi-square tests will be used to evaluate differences between the immediate intervention arm and delayed intervention control arm for couple-level continuous and categorical independent variables, respectively, to further characterize the sample of couples in the trial.

An intention-to-treat (full analysis) approach will be used to determine the comparison between groups based on the initial randomization and using outcomes for all randomized individuals. The primary analysis will be to compare the proportions of couples with outcomes A, B, and D in the immediate intervention versus the proportions of couples with similar outcomes in the delayed control arm using a chi-square test with one degree of freedom in a univariate analysis from the corresponding contingency table. The efficacy rate will also be presented as the ratio between binomial proportions with CIs estimated through conventional methods used for the couple-level measurement.

Longitudinal analyses will also be conducted [52-54], specifically for outcome C, relationship functioning variables, to explore changes over time and whether these changes differ by arm and by couples’ HIV serostatus. Specifically, generalized linear mixed-effects models (GLMMs) with SAS PROC GLIMMIX will be used to analyze the longitudinal data for outcome C from all 3 time points: baseline, 3 months, and 6 months after randomization. The analysis will fit a GLMM with fixed effects for time, a term for the pilot arm (immediate intervention vs delayed), and an arm-by-time interaction term. The GLMM will include random effects for the intercept and couple cluster (to account for within-couple correlation over time). Model fitting statistics will be used to determine the suitability of more parsimonious (eg, autoregressive) correlation structures and nonlinear effects for time. From the fitted GLMMs, the primary hypothesis will be examined by testing whether the coefficient of the group-by-time interaction term (the difference in slopes between immediate intervention vs delayed) is different from 0. The primary analysis will be performed at the couple level, with exploratory analyses performed at the individual level. For individual-level analyses, all models will use similar GLMMs with random effects to account for the intracluster correlation of couple members. We will also explore outcomes (A-D) at the individual level (n=120) by looking at each participant’s changes over time as secondary analyses of interest using multilevel models.

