#### Intention to Treat

An intention to treat approach [55-57] will be used to include all enrolled participants in the analysis. Any individuals or couples lost to follow-up will be assigned an adverse outcome (for outcomes A, B, and D) to be able to include them in the analysis. For outcome C, those lost to follow-up will have to be excluded as the outcome is continuous and there is no cutoff to determine an adverse outcome. This follows an intention-to-treat analysis plan where all randomized individuals are included in the final analysis independent of their participation after baseline assessment, which will also help ensure that the benefit of randomization to balance confounders is retained.

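### When only one partner answers at a visit, the primary couple-level model for outcome C leaves his score unused, against the stated intention-to-treat principle

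*Protocol article*

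**What the plan says.** All of this is in the Analytic Plan of the protocol article.

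- **Forming couple values (Primary Analyses).** "dyadic data will be calculated if there are no missing values from either partner". For continuous measures, "couple-level mean variables will be generated by taking the averaged value from both partners’ scores".
- **Level of analysis (Primary Analyses).** "The primary analysis will be performed at the couple level, with exploratory analyses performed at the individual level". The outcome C model is a generalized linear mixed model (GLMM) used to "analyze the longitudinal data for outcome C from all 3 time points: baseline, 3 months, and 6 months after randomization". The individual-level versions, with random effects for membership of a couple, are described separately.
- **Intention to treat.** Primary Analyses describes a comparison "based on the initial randomization and using outcomes for all randomized individuals". The Intention to Treat section says "all randomized individuals are included in the final analysis independent of their participation after baseline assessment", yet also states: "For outcome C, those lost to follow-up will have to be excluded as the outcome is continuous".
- **Relationship Dissolution.** Data from couples who break up stay in the intention-to-treat analysis by last observation carried forward.
- **Missing Data.** Attrition in the primary outcomes is referred back to the Intention to Treat section. The text then adds 25 multiple imputations within group, without saying whether men or couples are imputed. It also lists four parallel sensitivity models, one of them a GLMM on incomplete data.

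**The concern.** Read together, the both-partner rule and the couple-level primary analysis mean that a score a randomized man did provide is not used when his partner's is missing at the same visit. Two things are at stake.

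- **Precision.** A lone responder's score carries most of the information in a couple mean, and the rule gives it no weight.
- **Bias.** Whether a partner answers a relationship survey may well be related to how the relationship is going. The responding man's score at that visit is then the best available predictor of the missing one, and the rule discards it. The Missing Data section itself allows for more dropout in the delayed arm because of the wait, which is the situation in which the arm comparison would be distorted.

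The article also says these data will supply effect sizes for a later efficacy trial, so an avoidable bias would carry forward.

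**Working it through.** **1. The plan's own figure.** The article states 30 couples per arm and 80% power for 0.75 SD of the couple-level measure, at alpha 0.05 (taken as two-sided). A two-sample t-test needs 28.9, so 29 per arm; at 30 per arm power is 81.5%. The stated figure reproduces. It makes no allowance for missing couple values.

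**2. Share of couples affected.** The article gives no one-partner non-response rate, so the proportion m of men missing a visit is an assumption, with partners missing independently.

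- Both partners present: (1 − m)²
- Exactly one present: 2m(1 − m)

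**3. Information in a lone response.** A couple mean has variance σ²(1 + ρ)/2 and a single score has variance σ². One responder therefore holds (1 + ρ)/2 of a full couple's information: 60%, 70% and 80% at ρ = 0.2, 0.4 and 0.6.

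**4. Effective couples per arm and power at one visit (0.75 SD, ρ = 0.4).**

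- Both-partner rule: n = 30(1 − m)²
- All responders: n = 30[(1 − m)² + 2m(1 − m) × 0.7]

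| m | One responder only | Both-partner rule: n, power | All responders: n, power |
|---|---|---|---|
| 4% | 7.7% | 27.6, 78.2% | 29.3, 80.5% |
| 8% | 14.7% | 25.4, 74.5% | 28.5, 79.4% |
| 10% | 18.0% | 24.3, 72.6% | 28.1, 78.8% |

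For m = 10%: 30 × 0.81 = 24.3, and 30 × (0.81 + 0.18 × 0.7) = 28.1. The loss from the rule is 80.5 − 78.2 = 2.3 points at m = 4% and 78.8 − 72.6 = 6.2 points at m = 10%.

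**5. What the rule removes.** In an illustrative data set of 60 couples with 19% of follow-up couple values missing (1 − 0.9² = 0.19), the three-visit mixed model still used all 60 couples and 156 of 180 couple-visits. Only 38 couples had all three visits. The rule removes couple-visits, not couples.

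**6. Bias (illustrative simulations; all rates assumed).** There was no true effect and partner correlation was 0.5. Partner non-response was about 16% in the delayed arm, likelier when the responding man scored low, and 3% in the immediate arm.

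- One visit, complete dyads: difference of 0.12 SD.
- Couple means with baseline in the model: about 0.06 to 0.11 SD. A companion run gave 0.13, 0.11 and 0.07 SD at baseline-to-month-3 correlations of 0.3, 0.5 and 0.7.
- Individual records, all responders: 0.00 to 0.01 SD.
- With missingness made to depend on the absent man's own score: about 0.11 SD for individual records against 0.19 SD for complete dyads at one visit. With baseline used, the couple-level figure was 0.15 to 0.08 SD at within-man correlations of 0.5 to 0.8.

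In the scenario where the responding man's score drives non-response, low-scoring couples leave the delayed arm, so the bias flatters that arm and would hide benefit.

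**The case against.** **The couple is not lost.** A reader might infer that a couple with one responder is dropped from outcome C altogether. The documents do not support that. The rule makes one visit's couple value missing, and the GLMM keeps the couple through its other visits. Whole couples would go only if the exclusion in the Intention to Treat section were also applied to them. This objection stands and limits the point to couple-visits.

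**The rule may be descriptive only.** It appears in a paragraph on describing the sample, and the paragraph on the outcome C model does not repeat it. That model's random effects could be read as partner records nested in couples. Applying the rule to the model is therefore an inference. It is the natural one, because the same section makes the couple level primary and sets out individual-level models separately.

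**Remedies are already planned.** Multiple imputation, a GLMM on incomplete data and individual-level models all appear, so lone responders are analyzed somewhere. That is true, but not clearly in the primary analysis. Missing primary-outcome data are first sent back to a section that excludes them from outcome C, and the level of imputation is not given. A GLMM fitted to couple means inherits the same gap.

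**The size is assumed.** Partners may tend to miss together, which would shrink the one-responder share. The article reports 68 of 74 couples retained at month 6; split evenly, 34 per arm gives 86.1% power at 0.75 SD, so a claim that the trial falls short of its power would not be supported. The bias scenario is also the one in which an individual-record model does best. All of this stands.

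**A couple-level analysis suits a couple-level intervention.** It is legitimate. With complete dyads the two models give the same arm contrast, so the change gives nothing up.

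**Conclusion.** The point holds for couple-visits. As written, a lone responder's outcome C score is unused in the primary couple-level GLMM, which contradicts the stated use of outcomes from all randomized men. The sections on exclusion, last observation carried forward and imputation sit under one intention-to-treat label without settling what happens in this case.

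The cost in power is modest: about 2 to 6 percentage points at a single visit, if 4% to 10% of men miss it independently and the within-couple correlation is 0.4. Bias matters only if one-partner non-response differs by arm and is related to the outcome; in that case it can persist with baseline in the model. These sizes are ranges under assumptions, because the article does not give the rate. A reader might also infer that an individual-record model would be free of bias. It is so only when missingness depends on observed data; otherwise, in the single-visit check, it reduced the bias without removing it.

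The change should be made because it is cheap and uses data already collected.

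**What to change.** - Make the individual-record mixed model already described in Primary Analyses the primary analysis of outcome C: arm, time and arm-by-time as fixed effects, a couple random effect, a within-person term for repeated visits, and every available partner response.
- Keep the couple mean restricted to complete dyads as a sensitivity analysis.
- Bring Primary Analyses, Intention to Treat, Relationship Dissolution and Missing Data into line with one primary method for missing outcome C data, and state what is done when one partner responds. Do any imputation at the individual level, so that the responding man's score informs his partner's.
- Report by arm and visit how many couples had two, one or no responders.

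The cost is a swap of two analyses already planned and some redrafting. No new data are needed, and the arm contrast with complete dyads is unchanged.

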#### Aim 3: Preliminary Efficacy of the Intervention

Using the 6-month pilot RCT, this research will examine the preliminary efficacy of the intervention on couples: (A) formation and adherence to an HIV and STI prevention care plan containing evidence-based strategies (eg, ART for U=U, PrEP, and routine testing); (B) formation and adherence to a detailed sexual agreement, (C) relationship functioning (eg, mutual constructive communication and self-efficacy of decision-making and working together), and (D) self-reported and biomarker-confirmed indicators of vulnerability vis-à-vis sexual behaviors (eg, CAS) and HIV and STIs. The pilot RCT will have an allocation ratio of 1:1 and block randomization with a block size of 2, with blocks defined by dyad serostatus. Outcomes A and B will be dichotomous, outcome C will be continuous based on a bounded Likert scales, whereas outcome D will be a count variable based on STI incidence, HIV incidence, and CAS.

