#### Missing Data

Reminders and incentives will be used to maximize participation in the follow-ups. For the primary outcome measures, any missing data due to attrition would be handled as mentioned in the Intention to Treat section. In addition, missing data mechanisms [61-63] will be examined by comparing differences between the dropouts and the observed data. We will perform 25 conditional model-based multiple imputations within group using SAS PROC MI, and will aggregate the results into an overall group, time, and group-by-time interaction with SAS PROC MIANALYZE to provide unbiased intervention effects and their variances. This will also be advantageous if there is a differential dropout for the delayed condition due to wait time. To ensure the validity of the imputed data, 4 parallel models will be performed as a sensitivity analysis on (1) imputed data, (2) completers-only data, (3) assuming adverse outcome for those missing, and (4) applying GLMMs that have the advantage of handling incomplete unbalanced repeated-measures data by incorporating population average and subject-level trajectories, and in turn providing unbiased estimates of parameter of interests. If necessary, post hoc power analyses will be performed using the bootstrap method to calculate the observed power for the detected effect size.

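### Outcomes A to D all carry a primary label and are each tested at .05 with no lead outcome, so the plan does not say which result answers Aim 3; in this feasibility pilot the consequence is limited

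*Protocol article*

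**What the plan says.** Four places in the Analytic Plan of the protocol article bear on this.

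- Primary Analyses, on outcomes A, B and D: "The primary analysis will be to compare the proportions of couples with outcomes A, B, and D in the immediate intervention versus the proportions" in the delayed arm, each by a chi-square test with one degree of freedom.
- Primary Analyses, longitudinal paragraph, on outcome C: "the primary hypothesis will be examined by testing whether the coefficient of the group-by-time interaction term" differs from zero. The paragraph opens by presenting these models as a way to explore change over time and by arm, so C is worded both as exploratory and as primary. The section on Aim 3 describes C by examples, "relationship functioning (eg, mutual constructive communication and self-efficacy of decision-making and working together"), so it is more than one scale.
- Missing Data uses the plural: "For the primary outcome measures, any missing data due to attrition would be handled" as set out for intention to treat.
- Power, Sample Size, and Effect Size Estimations: "For all analyses, the α level was set at .05 with 95% CI". It claims 80% power separately for C (0.75 SD), for A and B (35 points) and for D (50% rate reduction).

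The article names no lead outcome, testing order or alpha split, and does not say how many of A to D must be positive. The section on Aim 3 places the comparison between arms from baseline to month 3.

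**The concern.** Aim 3 asks whether P3 shows preliminary efficacy on four outcome domains. If several tests are all primary and each uses the full .05, a significant result on any one of them can be presented as the primary finding. A mixed picture, such as C significant and A null, has no agreed reading. The chance of at least one false significant result then exceeds the stated .05. What is at stake is how Aim 3 will be reported, and the risk that the most favourable of several results gets the most attention when the later trial is planned.

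**Working it through.** **Inputs from the protocol article.** Alpha is .05 for every analysis, and there are 30 couples per arm. A, B and D have one chi-square test each. C has at least one arm-by-time test, and it is two-sided because the question is whether the "group-by-time interaction term (the difference in slopes between immediate intervention vs delayed) is different from 0". The effects are 0.75 SD for C and 35 points for A and B.

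**Inputs assumed.** The article gives no correlation between the test statistics, so I take one common value from 0 to 0.9. It gives no control proportion for A and B, so I vary it.

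**Step 1: reproduce the stated power.**
- Outcome C, normal approximation: 0.75 × √(30/2) − 1.96 = 2.905 − 1.96 = 0.945, which gives 82.8%. The t test gives 81.5%.
- Outcomes A and B, 35-point difference: 81.6% for 20% vs 55%, 79.9% for 25% vs 60%, and 78.9% for 32.5% vs 67.5%, which is the least favourable case.

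Both claims of 80% reproduce with the whole two-sided .05 spent on each test, so the sample size holds no allowance for multiplicity. The power for D cannot be checked because no base rate is given.

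**Step 2: error rates for four tests under a global null, if independent.**
- At least one significant in either direction: 1 − 0.95⁴ = 18.5%.
- At least one significant in favour of P3: 1 − 0.975⁴ = 9.6%.
- Single two-sided test: 5% in either direction, 2.5% in favour.

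**Step 3: allow for correlation.** I simulated 500,000 sets of equally correlated standard normal statistics, oriented so that positive favours P3. I counted sets with any |z| > 1.96 and sets with any z > 1.96.

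| Tests | Correlation | Either direction | Favouring P3 |
|---|---|---|---|
| 4 | 0 | 18.5% | 9.6% |
| 4 | 0.5 | 15.5% | 7.8% |
| 4 | 0.8 | 11.5% | 5.8% |
| 4 | 0.9 | 9.4% | 4.7% |
| 6 | 0 | 26.5% | 14.1% |
| 6 | 0.5 | 20.9% | 10.5% |
| 6 | 0.8 | 13.9% | 6.9% |

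The six-test rows count three C scales separately. That is one reading of the examples in the Aim 3 section, which fixes no number. With four tests and correlations of 0 to 0.8, the false favourable rate is 5.8/2.5 = 2.3 to 9.6/2.5 = 3.8 times that of a single test.

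**Step 4: check the nominal size.** The exact size of the chi-square test with 30 per arm is 4.9–5.4% at the event rates tried from 10% to 50%, but 2.8% at an event rate of 5%. A rare outcome D would lower the figures slightly.

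**Step 5: compare remedies.** One named primary at .05 keeps the stated power. A four-way Bonferroni split (.0125 each) cuts power to 63% for 0.75 SD (t test). For 35 points it falls to 63% at a control proportion of 20% and to 59% at 32.5%.

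**The case against.** The strongest reply is that this is a pilot. Efficacy is called preliminary throughout and is the third aim, after feasibility and acceptability. The power section says the trial can detect only large effects. No decision depends on a p-value, and the Conclusions present the full trial as the expected next step without making it conditional on significance. Family-wise error control is not normally required in such a study. Testing order and multiplicity are also commonly left to a statistical analysis plan, which is not shown here. Finally, the longitudinal paragraph words C as exploratory, so the four outcomes are not plainly equal in rank.

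Most of this stands, and it limits the consequence. It does not remove the point. The article does not merely leave the ranking open. It calls the tests of A, B and D primary, attaches the primary hypothesis to C, speaks of primary measures in the plural and gives each test a .05 threshold. The double wording of C is part of the inconsistency. An analysis plan that already names a lead outcome would settle the matter, and the article's labels would then need to match it.

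**Conclusion.** The point holds in a limited form. The article labels several couple-level tests primary at full alpha and does not say which one answers Aim 3. With four two-sided tests and no true effect, at least one is significant in either direction about 11–19% of the time, and at least one falsely favours P3 about 6–10% of the time, against 2.5% for a single test. Both ranges rest on assumed equal correlations of 0.8 to 0; a higher correlation gives less.

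Three stronger readings are tempting but not supported:

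- That 11–19% is the rate of false efficacy findings. It includes results against P3; the favourable share is about half.
- That D adds three separate primary tests, for STI, HIV and CAS. The article says "outcome D will be a count variable based on STI incidence, HIV incidence, and CAS" and powers one combined STI rate that includes HIV. No separate primary tests are planned.
- That the later trial will be justified or sized from whichever test comes out largest. The section on Aim 3 says sizing will draw on data pooled from both arms, and no rule selects among significant results.

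This is a correction worth making, but it does not invalidate the pilot.

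**What to change.** In Primary Analyses, name one lead efficacy contrast. An example is outcome A at couple level, immediate vs delayed arm at month 3, tested two-sided at .05. Month 3 closes the randomised comparison window. The choice of A is open to the investigators, since the Objective links the care plan to the sexual agreement and so touches B as well. Report B, each C scale and D as secondary or preliminary, with effect estimates and 95% CIs and no claims of significance. Remove the primary-hypothesis wording from the paragraph on C.

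An acceptable alternative is to label all comparisons of A to D preliminary and report only estimates with CIs.

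In either case, show the estimates for every outcome when planning the later trial, so that none is chosen for its size. This leaves the stated pooled estimation in place.

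The cost is a few sentences, with no new data, and a lead outcome tested at .05 keeps its stated power. The downside is that a significant B, C or D alone can no longer be presented as a primary finding. The article reports that data collection ended in April 2024 and that analysis is under way. The choice should therefore be documented before results by arm are seen, or disclosed as post hoc.
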